## Methods

### Sampling Frame

#### Study Design

This is an observational study that will involve collecting cross-sectional survey data from a national sample of students, teachers, and principals from 12 secondary public schools across the United States. Our sample includes participants from 6 randomly selected exposure schools: secondary schools that have recently experienced an intentional school shooting (<2 years ago) and secondary schools that have experienced an intentional school shooting less recently (>2 years ago). Of the schools in our dataset that meet these criteria, we are randomly selecting schools to participate in our study from the group of eligible schools. If a school does not express interest in participating, we are replacing that school with another eligible school in our dataset. We are then matching our exposure schools to 6 randomly selected nonexposure schools: 6 secondary public schools that have never experienced a school shooting. We are matching the nonexposure schools to exposure schools on the following key variables: state, urban or nonurban status, and school level (ie, middle or high school).

#### Exposure School Selection

Our research team is identifying all possible intentional school shooting cases via a comprehensive review of multiple national school shooting databases, including the K-12 School Shooting database, the Everytown for Gun Safety database on gunfire on school grounds, and the Washington Post database on school shootings, to identify all schools that have experienced intentional gunfire on campus during school hours [51]. These data document all incidents in which a gun is fired or a bullet hits school property for any reason, regardless of the number of victims, time, or day of the week. Our research team is then coding this list of incidents to identify cases that meet the criteria for intentional school shooting at a secondary (ie, middle or high school level) public school—all cases of intentional gunfire on school property, occurring during school hours (including 1 hour before official school activities begin and 1 hour after all official school activities end), beginning January 1, 2015—to ensure we have enough schools in our sampling frame that meet our aforementioned criteria. We are excluding accidental discharges and attempted suicides where no other person was targeted or shot. We are also excluding any incidents taking place on a school bus and on school property that are noncontiguous with the school’s primary campus. Furthermore, we are cross-referencing our list of incidents with other publicly available data sources [40] to ensure that no incidents meeting our criteria are missed. Two members of our research team are then independently coding this list of incidents to identify the cases that meet our proposed study’s criteria for “intentional school shooting”; a third member of our study team is reviewing any potential discrepancies in coding efforts. The final list of exposure schools will then be divided into 2 based on recentness, that is, schools where the incident happened between January 1, 2015, and December 31, 2021, and schools where the incident happened between January 1, 2022, to December 31, 2023. In total, 3 schools will be randomly selected from each list. In case a school declines to participate, we will move to the next randomly selected school. Nonexposure schools will be matched to the final exposure schools. In case a school declines to participate, we will move to the next randomly selected school.

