#### Recentness

To operationalize the “recentness” of a school shooting event, we considered the existing literature on posttraumatic stress. The evidence shows that the onset of posttraumatic stress disorder (PTSD) symptoms can vary drastically (eg, symptoms may appear within 3 months of the traumatic experience or be delayed by months or even years) [52-54]. A 2-year cutoff, therefore, allows us to assess the difference between a more immediate impact versus a longer-term impact on youth mental health outcomes. Similarly, we expect shifts in perceived school safety, school safety strategies, and the implementation of other related school initiatives and programs to vary considerably in the aftermath of a school shooting incident. The 2-year cutoff will allow us to compare schools in the midst of that “flux” to those schools that have had some time to adapt their practices and policies following exposure to such violence.

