## Results

IRB approval for this research project was obtained and the study subsequently began its recruitment and data collection phase in January 2024. Data collection is currently ongoing, and the expected completion date is January 2025. As of May 2024, we have recruited and administered the surveys at 3 secondary public schools. The full data analysis is expected to be completed by August 2025.

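### The fixed 2022-2023 incident list matches the stated under-2-years definition of a recent shooting only at 1 January 2024, while surveys run to January 2025

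*Protocol article*

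**What the plan says.** Study Design describes two kinds of exposure school. The recent kind is given as "secondary schools that have recently experienced an intentional school shooting (<2 years ago"). The other kind lies on the far side of the same boundary: "secondary schools that have experienced an intentional school shooting less recently (>2 years ago"). The Methods part of the Abstract uses the same two labels. Recentness gives the reason for the boundary: "A 2-year cutoff, therefore, allows us to assess the difference between a more immediate impact versus a longer-term impact". It adds that schools soon after an incident are still changing their practices, whereas others have had time to adapt.

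Exposure School Selection turns this into two lists with fixed dates. The less recent list holds "schools where the incident happened between January 1, 2015, and December 31, 2021" and the recent list holds "schools where the incident happened between January 1, 2022, to December 31, 2023". The draw is equal: "In total, 3 schools will be randomly selected from each list".

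Results puts the start of recruitment and data collection in January 2024 and says: "Data collection is currently ongoing, and the expected completion date is January 2025". By May 2024, 3 schools had been surveyed. The Data Analysis Plan compares students, and separately teachers, across three levels: more recent, less recent and never. Independent Covariates lists time since the shooting among the covariates. The article states no reference date for counting the 2 years and no rule for reassigning a school according to when it was surveyed.

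**The concern.** The label and the sampling rule define different groups for almost the whole survey period. Symptoms, well-being and perceived safety are measured once, at the survey. A cutoff justified by immediate versus longer-term impact therefore has to refer to the interval from incident to survey. A fixed calendar window cannot hold that interval under 2 years when surveys are spread over about 12 months after the window closes.

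At stake is what the recent versus less-recent contrast can be said to show. There are only 3 schools in the recent group, so a single school beyond 2 years is a third of it. A result reported as the effect of a shooting within the past 2 years could rest partly on schools up to about 3 years out.

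**Working it through.** **Inputs from the protocol article**
- Recent window: 1 January 2022 to 31 December 2023, which is 365 + 365 = 730 days (Exposure School Selection).
- Less recent window: ends 31 December 2021 (same section).
- Stated boundary: 2 years (Abstract, Study Design, Recentness).
- Survey period: January 2024 to January 2025 (Results).
- Schools drawn from the recent list: 3 (Exposure School Selection).

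**Assumption not in the article:** incident dates are spread evenly over the window. Individual incident and survey dates are not given.

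**Step 1. Reproduce the plan's label.** Share of the window more than 2 years old = (survey date minus 2 years, minus 1 January 2022) / 730. For a reference date of 1 January 2024 this is 0/730 = 0%. The list and the label agree exactly at that date.

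**Step 2. Move the reference date through the survey period.**

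| Survey date | Days over 2 years | Share of 730 |
|---|---|---|
| 1 January 2024 | 0 | 0% |
| mid-January 2024 | 14 | 2% |
| mid-May 2024 | 134 | 18% |
| mid-September 2024 | 257 | 35% |
| 1 January 2025 | 365 | 50% |
| mid-January 2025 | 379 | 52% |
| 31 January 2025 | 395 | 54% |

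**Step 3. Oldest incident.** An incident on 1 January 2022 is 3.0 years old at a survey on 1 January 2025 and 3.1 years old on 31 January 2025.

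**Step 4. Average over the survey period.** If survey dates are also spread evenly, the average share is 24.9% for surveys to 31 December 2024 and 27.0% for surveys to 31 January 2025. The expected number among the 3 recent schools is 3 × 0.249 = 0.75 to 3 × 0.270 = 0.81. Treating the 3 schools as independent, the chance that at least one is beyond 2 years is 1 − (1 − 0.249)³ = 0.58 to 1 − (1 − 0.270)³ = 0.61.

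**Step 5. The other list.** The latest incident on the less recent list, 31 December 2021, is already 2.0 years old on 1 January 2024. Every school on that list is therefore correctly labelled at any survey date. The mismatch can arise only in the recent group.

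**The case against.** The strongest reply is that the 2022-2023 window is exactly the 2 years before data collection began. A random draw needs a closed list, and fixed dates make the draw reproducible. On that reading the under-2-years label is shorthand for time at study start, and only a sentence naming the reference date is missing. This stands as an explanation of how the list arose, but the article does not say it, and the rationale in Recentness fits time at survey better.

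A second reply is that time since the shooting is already a planned covariate. That is true, and it means elapsed time is meant to be collected. It does not change the group labels used in the three-level comparison, and it has no value for schools that never had a shooting.

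Three stronger readings are tempting, and the article does not support them:
- **Bias toward no difference.** Contamination runs one way, so a reader might infer that the contrast is diluted. Recentness itself says that symptom onset varies widely and can be delayed by years. A school at 25 to 36 months need not resemble the older group, and with 3 schools per list one school could move the contrast in either direction.
- **Most recent schools surveyed late.** Only 3 of 12 schools had been surveyed by May 2024, but 6 of the 12 are nonexposure and 3 are less recent. Nothing says when the 3 recent schools were or will be surveyed, and the number affected may be zero.
- **Incidents in 2024 misclassified.** They fall on neither list because the frame was closed before sampling. Those schools are unsampled, not mislabelled.

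**Conclusion.** The inconsistency is real and limited in scope. The stated definition and the sampling rule agree only at 1 January 2024 and diverge steadily afterwards, until about half of the recent window is more than 2 years old in January 2025. The half is a latest-date figure. The average of 25-27%, or about 0.8 of 3 schools, is the fairer summary, and it rests on evenly spread incident and survey dates. These are shares of a calendar window, not counts of actual schools.

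The comparison of schools with and without a shooting, which the first research question poses, is unaffected because every incident on either list remains an exposure. What needs correcting is the claim attached to the recent versus less-recent contrast.

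**What to change.** Keep the lists as drawn and change three things.

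1. Replace the under-2-years and over-2-years labels throughout with the calendar windows: recent means an incident in 2022-2023, up to about 3 years before survey; less recent means an incident in 2015-2021.
2. Compute months from incident to survey for each exposure school and report them. Both dates are knowable for every school, and the time-since-shooting covariate already calls for much the same quantity.
3. Repeat the recent versus less-recent comparison of the Data Analysis Plan with schools classified at 24 months by survey date.

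The cost is wording, one derived variable and one further analysis, with no new data. Full analysis is not due until August 2025.

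The downside lies in the third step: the 3/3 split may become 2/4 or more uneven. With a 25% share per school, the chance that two or all three recent schools move, leaving 1/5 or 0/6, is 3 × 0.25² × 0.75 + 0.25³ = 0.16. With a 52% share it is 3 × 0.52² × 0.48 + 0.52³ = 0.53. The contrast may then not be estimable, so the reclassified comparison should stand beside the comparison by calendar window and not replace it.

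Redrawing the recent list on a rolling 24-month window is not advisable. It would change the sampling frame after schools have been surveyed, so that early and late schools would come from different populations.

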#### Recentness

To operationalize the “recentness” of a school shooting event, we considered the existing literature on posttraumatic stress. The evidence shows that the onset of posttraumatic stress disorder (PTSD) symptoms can vary drastically (eg, symptoms may appear within 3 months of the traumatic experience or be delayed by months or even years) [52-54]. A 2-year cutoff, therefore, allows us to assess the difference between a more immediate impact versus a longer-term impact on youth mental health outcomes. Similarly, we expect shifts in perceived school safety, school safety strategies, and the implementation of other related school initiatives and programs to vary considerably in the aftermath of a school shooting incident. The 2-year cutoff will allow us to compare schools in the midst of that “flux” to those schools that have had some time to adapt their practices and policies following exposure to such violence.

#### Nonexposure School Selection

To select the nonexposure schools, we are randomly selecting 6 schools from a database of all public secondary schools in the United States [55], matching for the aforementioned variables (ie, state, urban or nonurban, and school level).

#### Students

Within each participating school, all students between grades 6 to 12 are eligible for and invited to participate in this study. To encourage study participation, we are implementing reasonable incentives for participants, keeping the survey as brief as possible, communicating study expectations clearly and consistently, engaging thoughtfully with each school’s leadership team during the recruitment process, and using other best practices [56,57]. Accounting for attrition and individuals choosing not to participate, we expect a 15% to 20% response rate (which is consistent with other research that has involved collecting survey data directly from students, teachers, and principals) [58,59], and therefore, anticipate sampling between 1000 to 1200 students across the 12 participating schools.

#### Teachers

Within each participating school, all teachers are eligible for and invited to participate in this study. Multiple efforts are being made to maximize participant recruitment and retention. We anticipate a minimum of 60 teachers and upward of 120 teachers (5-10 teachers per school, on average) to participate in this proposed study.

#### Principals

The current principal of each school is eligible and being invited to participate in this study.

### Participant Recruitment

#### Recruitment Process

In mapping out the study’s recruitment process, the project team has drawn on existing best practices to ensure the study’s success. First, the project team defined a clear sampling frame for school recruitment to ensure that the 12 schools being recruited fall within the purview and meet the purpose of the study’s aims. We are also providing reasonable and feasibly budgeted incentives for all participating schools (specifically, a US $250 gift certificate to Amazon) as a small way to appropriately recognize each school’s time and commitment to this study effort. To ensure that this effort takes only minimal time away from the existing school day and does not detract from the various responsibilities of all participants, the project team has worked to ensure that each aspect of the data collection process is as brief and efficient as possible. All of these details are being conveyed to the potential participating schools during the recruitment process.

#### Principal and Teacher Recruitment

In line with best practices, the principal at each potential participating school within our sampling frame is being approached directly through a written letter (sent via email). After 2 weeks, and if there is no response, the co–principal investigators (co-PIs) of the study are following up through a telephone call. The co-PIs are then meeting with the principal via Zoom (Zoom Video Communications, Inc) at their convenience to engage with them and describe the processes and expectations of the study for the school’s participation, as well as the corresponding risks and benefits, and provide opportunity for the principal to ask questions (with additional opportunity for further conversations, as needed). If the principal agrees to support the study effort, the co-PIs are working closely with each principal to then recruit the school’s teachers and students for participation in the study. The project team’s previous research experience conducting this kind of research suggests that this engagement approach is beneficial for participant recruitment and aims to ensure participant comfort and transparency with all aspects of the study protocol.

To maximize principal and teacher participation, the co-PIs are organizing an optional 30-minute recruitment meeting initially via Zoom at each school (to be scheduled, with the principal’s support, during the school’s professional development hours). During this time, the co-PIs are presenting an overview of the study’s purpose and proposed methods, highlight any relevant risks and benefits (including provision of incentives), describing the informed consent process, and providing an opportunity for the principal and teachers to ask questions about the study itself.

It should be emphasized that participation in this study is relatively brief and will involve the completion of 1 web-based survey. The informed consent form will be included at the beginning of the survey. However, as noted above, part of the recruitment meeting will involve the co-PIs answering any questions about the study and its corresponding informed consent process.

#### Student Recruitment

Similarly, to maximize student participation, the co-PIs are organizing an optional 30-minute recruitment meeting via Zoom for the students and their parents at each school. During this time, the co-PIs will present an overview of the study’s purpose and proposed methods, highlight any relevant risks and benefits (including provision of incentives), describe the informed consent process, and provide an opportunity for the students and parents to ask questions about the study itself. Again, during this time we are emphasizing that participation is relatively brief and will involve the completion of 1 web-based survey. The informed consent form is also being included at the beginning of the survey (and for students older than 12 years, this will also include an assent form). As noted earlier, part of the recruitment meeting will involve the co-PIs answering any questions about the study and its corresponding informed consent process.

### Measures

#### Data Collection Overview

This study involves collecting cross-sectional survey data from students, teachers, and principals from 12 public secondary schools across the United States. Publicly available secondary data about each school will also be collected and used. All participants will complete the survey on the web.

#### Demographics

Data on sex, race, age, grade-level, and presence or not at the time of the school shooting incident for students in the exposure school will be provided by each student at the beginning of the survey. Self-report data on teacher and principal demographics (eg, their length of time working at the school) will also be collected at the beginning of the teacher and principal surveys, respectively.

#### Mental Health and Well-Being

Among the participating students in each school, self-report data on mental health and well-being will be assessed via a survey that comprises items from the following: (1) the Patient Health Questionnaire (PHQ)–A [60], a validated and widely used survey assessing mental health and symptoms of depression among the youth; (2) the Child and Adolescent Trauma Screen [61], which has been validated for use by young people aged 7 to 17 years; and (3) the World Health Organization Well-Being Index (WHO-5) [62], which has been validated for use by individuals 9 years and older. The PHQ-A and Child and Adolescent Trauma Screen items are multiple-choice with 4 response options, and the WHO-5 items are rated on a 6-point Likert scale [60-62].

Among the participating teachers in each school, self-report survey data on mental health and well-being will be assessed via items from the following: (1) the PHQ-9 [63], a validated scale assessing mental well-being and symptoms of depression among adults; (2) the Generalized Anxiety Disorder-7 scale [64], which has also been validated and assesses the most common anxiety disorders among adults; and (3) the WHO-5 [62]. The PHQ-9 and Generalized Anxiety Disorder-7 items are multiple-choice with 4 response options, and the WHO-5 items are rated on a 6-point Likert scale [62-64].

#### ACE and PCE Prevalence

Each student will provide self-report data on ACE and PCE prevalence. The ACE items were adapted in previous research [17] from a validated tool [19]. Building upon additional research that has argued that children experience a greater range of adversity than most ACE assessments currently capture [31,33], additional items will be included. The survey will, therefore, assess the following: bullying, residential instability, meeting of basic needs, divorced parents, family member with poor mental health, family member engaging in substance use, domestic violence, incarcerated parent, community violence, exposure to gun violence, and exposure to violence in school. Each item will be multiple-choice, with the following response options: “yes,” “no,” or “prefer not to answer,” and these data will comprise an ACE prevalence score that denotes how many ACEs each student has experienced. PCE items were similarly adapted in previous research [34].

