**Conclusions:**

The results from this study promise to generate meaningful and novel findings on the extent to which having a prior history of ACEs moderates the relationships among exposure to intentional school gun violence, school safety strategies, and student outcomes (ie, mental health and well-being, and perceptions of school safety).

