### Purpose

Poor mental health symptoms and ACEs among the youth predict extensive co-occurring adverse outcomes, including increases in long-term risk for chronic disease and injury, impaired child development, and poor academic outcomes [17-20]. At the same time, the anticipation of school shootings has fueled school safety and security interventions that may inadvertently increase anxiety, depression, and other indicators of poor mental well-being among students and staff alike [29,50]. Despite this, the association between exposure to existing school safety interventions and student mental health outcomes, particularly beginning in early adolescence, is not clear. It is also unclear whether, how, and to what extent the strength of these associations might differ among students and staff members from those schools that have more recently experienced a school shooting, those that have experienced a school shooting less recently, and those that have never directly experienced a school shooting but are nonetheless indirectly aware of these tragic events via media and other networks. Finally, we do not know whether and to what extent having a prior history of ACEs moderates the relationships among exposure to school shootings, exposure to school safety strategies, and student outcomes (eg, perceptions of school safety and academic achievement). The role of PCEs is also unknown. This study therefore seeks to fill these critical research gaps by answering the following questions:

Is there a significant difference in the prevalence of mental health outcomes, perceived school safety, and academic engagement between early adolescent and adolescent students (grades 6-12) at public secondary schools that have experienced a school shooting and those that have not?Are existing interventions to promote school safety and security associated with poor mental health outcomes among students and school staff members?Does the strength of this association between school safety interventions and mental health outcomes differ among students and teachers who have experienced an intentional school shooting versus students and teachers who never experienced a school shooting? Furthermore, are these associations moderated by student ACE history?

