### Data Analysis Plan

The data collected from the students, teachers, and principals across all 12 participating schools will be analyzed and will fully respond to each of the research questions. Descriptive statistics will be calculated to summarize student and teacher participant characteristics within each school and also describe each school’s safety and security strategies. Analyses of covariance will subsequently be used to identify potential significant differences in the prevalence of mental health and well-being, perceptions of school safety, educational outcomes, and ACEs among students in schools that have more recently experienced an intentional school shooting, schools that have experienced an intentional school shooting less recently, and schools that have never experienced a shooting, while controlling for key covariates.

ANOVA will also be used to identify potential significant differences in the prevalence of mental health and perceptions of school safety among teachers in schools that have more recently experienced an intentional school shooting, schools that have experienced an intentional school shooting less recently, and schools that have never experienced an intentional school shooting. We used G^*^Power (version 3.1; Heinrich Heine University Düsseldorf) to run power analyses in anticipation of our proposed analyses, assuming an α level of .05 and a power of 0.80. In the case of our proposed student analyses, a very small minimum effect size will need to be detected to meet our power requirements and given our anticipated minimum sample size (exposure schools: N=500-600, nonexposure schools: N=500-600). In the case of our teacher analyses, a medium effect size will need to be detected and given our anticipated minimum sample size (exposure schools: N=30-60, nonexposure schools: N=30-60). On the basis of the average enrollment across secondary public schools in the United States, we should be able to reach the minimum sample size from 12 schools.

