Multiple regression analyses will then be used to determine if the strength of the association between school safety interventions and mental health outcomes differs among students and school staff in schools with varying levels of trauma exposure. Mediated moderation analyses will evaluate the role of ACEs on the relationships between exposure to an intentional school shooting, exposure to school safety strategies, and student outcomes (ie, mental health and well-being, perceptions of school safety, and educational outcomes) [78]. Again, power analyses revealed that for our student-level analyses and given an α level of .05 and a power of 0.80, a small effect size will need to be detected to meet our power and sample size requirements. In the case of our proposed teacher analyses, a medium effect size will need to be detected. It should be noted that these values reflect conservative estimates with regard to student and staff recruitment. Thus, we are confident that we will achieve reasonable power to fully answer all of our questions and achieve the specific aims of the study.

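### Two of the 11 items in the ACE score can be answered yes because of the index shooting, so the score used as moderator is not a clean measure of prior ACE history

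*Protocol article*

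**What the plan says.** The ACE and PCE Prevalence section lists 11 topics for yes/no/prefer-not-to-answer items. The last three are "community violence, exposure to gun violence, and exposure to violence in school". It then fixes the scoring: "these data will comprise an ACE prevalence score that denotes how many ACEs each student has experienced". No item is left out, and no reference period or exclusion of the index shooting is stated.

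The score has two uses in the Data Analysis Plan. Analyses of covariance compare "educational outcomes, and ACEs among students in schools" with a recent, a less recent or no shooting. The plan also says that "Mediated moderation analyses will evaluate the role of ACEs on the relationships between exposure to an intentional school shooting, exposure to school safety strategies", with outcomes in students as the third element.

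The intended meaning of the moderator is given elsewhere. The Purpose section says it is unknown whether "having a prior history of ACEs moderates the relationships among exposure to school shootings, exposure to school safety strategies, and student outcomes", and its last research question asks "are these associations moderated by student ACE history". The Abstract's Conclusions again speak of "having a prior history of ACEs moderates the relationships among exposure to intentional school gun violence".

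Three further facts matter. The design is a single cross-sectional survey (Study Design). The exposure is intentional gunfire on school property around school hours (Exposure School Selection). Each student in an exposure school reports whether he or she was present at the incident (Demographics), but that answer is not tied to the ACE score.

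**The concern.** A student who was at school during intentional gunfire can truthfully answer yes to both the gun-violence item and the school-violence item because of that one event. The Abstract's Background itself classes intentional school gun violence as an ACE. The 11-item count can therefore contain the exposure that it is meant to moderate, and it is collected after that exposure.

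Three readings are at stake:

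- **Moderation by prior ACE history.** Part of the score may not be prior.
- **The ACE comparison between exposure groups.** Exposed students may score higher because of the shooting, not because they started with more adversity.
- **The shooting effect at a given ACE score.** An exposed student with a score of 4 may have the prior history of an unexposed student with a score of 2 or 3. Comparing the two at equal scores removes part of the effect under study.

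**Working it through.** The documents give no ACE mean, standard deviation or interaction effect, so there is no figure of the plan's own to reproduce. The check has two parts: how far the score can move, and what that does to a linear moderation model.

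**Inputs from the protocol article.** There are 11 items, two of which overlap with the exposure. The planned sample is 500 to 600 students per exposure group, and α is 0.05.

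**Assumed inputs, not in the documents.** Each of the other nine items has 20% prevalence. Background yes is 10% for gun violence and 30% for school violence (0% in the simplest case). The shooting effect is 0.30 SD in students who were present, and the ACE slope is 0.15 SD per item. The true interaction is 0 or 0.10 per item. The share present runs from 0% to 100%, and absent students do not answer yes because of the shooting.

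**Step 1: shift in the group mean.** Let p be the share present, y the share of those who answer yes because of the shooting, and b the background yes. Each overlapping item then shifts by p × y × (1 − b). With b = 0.10 and 0.30, the two items together shift by p × y × (0.90 + 0.70) = 1.60 × p × y.

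- All present, y = 1, no background yes: 1 + 1 = 2.00
- All present, y = 1: 1.60
- All present, y = 0.7: 1.60 × 0.7 = 1.12
- 50% present, y = 0.9: 1.60 × 0.45 = 0.72
- 25% present, y = 0.9: 1.60 × 0.225 = 0.36
- None present: 0.00

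**Step 2: uniform shift.** Suppose every exposed student's score rises by s. Write the ACE slope as β and the interaction as γ. The exposure effect at a given score then falls by s × (β + γ), and the interaction stays at γ. With s = 2, β = 0.15 and γ = 0, a true 0.30 becomes 0.30 − 2 × 0.15 = 0.00. With γ = 0.10 it becomes 0.30 − 2 × 0.25 = −0.20, so the effect can pass zero. The interaction is unaffected in both cases.

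**Step 3: non-uniform shift.** This was simulated with 500 students per group, 2,000 data sets and clustering ignored. The outcome was regressed on exposure, ACE score and their product, and the exposure effect was read at a score of 2. In the table the true interaction is 0.

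| Present | Yes among present | Background yes (gun / school) | Shift in mean score | Exposure effect: true → 11-item score | Interaction obtained | Rejection at 5% |
|---|---|---|---|---|---|---|
| 100% | 100% | 0% / 0% | 2.00 | 0.30 → 0.00 | 0.00 | 5.1% |
| 100% | 100% | 10% / 30% | 1.60 | 0.30 → 0.06 | 0.00 | 5.6% |
| 100% | 70% | 10% / 30% | 1.12 | 0.30 → 0.16 | −0.02 | 7.6% |
| 50% | 90% | 10% / 30% | 0.72 | 0.15 → 0.03 | 0.01 | 6.1% |
| 25% | 90% | 10% / 30% | 0.36 | 0.08 → 0.02 | 0.01 | 6.0% |
| 0% | – | 10% / 30% | 0.00 | 0.00 → 0.00 | 0.00 | 5.3% |

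The true group effect falls with presence because only present students carry it (0.50 × 0.30 = 0.15; 0.25 × 0.30 = 0.075).

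With a true interaction of 0.10 and all students present, full endorsement leaves it at 0.10. With 70% endorsement it falls to 0.06, and power drops from 54% to 25%. With 25% or 50% present, the interaction changes by at most about 0.01.

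**Step 4: comparison scores.** In the same runs, a score limited to prior events recovers the true exposure effect and interaction. The nine-item score shows a group difference of 0.00. The nine-item score was not itself run through the regression.

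**The case against.** The other side has a good deal to say, and much of it stands as a limit on size.

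A reader might infer that exposed schools score higher by construction, because their students will answer yes to both items. The documents do not support that. Three of the six exposure schools come from incidents in 2015 to 2021, and data collection began in January 2024. Assuming ordinary grade spans (6–8 and 9–12), a high-school student surveyed in spring 2024 enrolled no earlier than autumn 2020, and a middle-school student no earlier than autumn 2021. For most of that window no current student was enrolled. The source databases also count gunfire regardless of the number of victims, so not every student present need answer yes. The overlap acts through students who were present at or report the event, not through whole schools.

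A reader might also infer that the moderation result cannot be read at all. That goes too far. A uniform shift leaves a linear interaction slope unchanged, and in the partial-presence cases the slope hardly moves. In addition, part of the question concerns moderation of the safety-strategy association, which has no built-in identity with the two items.

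The between-group comparison is not wrong in itself. The protocol deliberately counts gun violence as an ACE, and total ACE burden by school type is a fair description. It becomes circular only when read as prior adversity.

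Exact item wording is not shown. Wording that excluded the index shooting would shrink the problem, but nothing in the article says that it does.

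Finally, the Data Analysis Plan's term, mediated moderation, may look like a further error beside a question about moderation. The item overlap does not establish that, and it is no part of this point.

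**Conclusion.** The concern holds in a limited form. The article fixes the score as a count of all 11 items, asks about prior ACE history, and measures ACEs after the shooting. Nothing separates the index event from the two overlapping items. This is a fault in what is stated, not a detail left to a fuller plan.

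Three consequences follow for students who were present at or report the event. The group comparison of ACEs is partly circular if read as prior adversity. The shooting effect at a given ACE score is biased downward when more ACEs go with worse outcomes: toward zero, or past it if there is also a positive interaction. The interaction is distorted when endorsement varies among exposed students, and this was appreciable only in the case with all present and 70% endorsing.

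The artefact in the group mean is 0 with none present, about 0.4 ACE with 25% present, and at most 2 ACEs. These sizes rest on assumed prevalences, endorsement rates, slopes and shares present, and on independent students. The documents supply none of these values.

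**What to change.** Before analysis, define a nine-item ACE score that omits the gun-violence and school-violence items. Use it as the moderator and in any between-group comparison read as prior adversity. Keep the 11-item count to describe total ACE burden, and repeat the moderation analyses with it as a sensitivity analysis. Use the presence-at-incident answer to show how far the two scores differ among exposed students who were and were not there.

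The items are answered separately, so this needs only rescoring and a change of wording, with no new data. There is a price. Genuine gun or school violence unrelated to the index shooting drops out of the moderator, and the score is less comparable with broader ACE counts. The nine items also do not date the remaining ACEs, and they keep community violence, which some students might answer with the shooting in mind. The change removes the plain overlap but does not make every item demonstrably prior.
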